### Withdrawal and discontinuation criteria

At any time, subjects are free to withdraw from the study (investigational product and assessments), without prejudice of further treatment (withdrawal of consent). The reason(s) for withdrawal and the presence of any AEs will be investigated.

Patients who withdraw consent for further participation will not receive any further investigational product or further study observation, with the exception of follow-up for survival, which will continue until the end of the study unless the patient has expressly withdrawn his or her consent to survival follow-up.

Subject will be considered lost to follow-up only if no contact has been established by the time the study is completed such that there is insufficient information to determine the subject’s status at the time.

Reasons that will lead to permanent investigational product discontinuation are detailed in Table 3. Any patient who has not yet shown objective radiological disease progression at withdrawal from investigational product should continue to be followed as per RECIST 1.1.

**Table 3 Tab3:** Criteria for permanent discontinuation of investigational product

Discontinuation criteria - Investigational product	
1 Patient weight falls to 30 kg or less.	
2 Withdrawal of consent to participate in the study or lost to follow-up.	
3 Withdrawal of consent for further treatment with investigational product.	
4 Adverse event that, in the opinion of the investigator or the sponsor, contraindicates further dosing.	
5 Patient who will probably meet one or more exclusion criteria at study entry, to whom pursuing investigational therapy might constitute a safety risk.	
6 Pregnancy or intent to become pregnant.	
7 Any AE that meets discontinuation criteria.	
8 Grade ≥ 3 infusion reaction to durvalumab or tremelimumab.	
9 Patient non-compliance that, in the opinion of the investigator or sponsor, warrants withdrawal.	
10 Initiation of alternative anticancer therapy including another investigational agent.	
11 Confirmation of PD and no benefit from treatment with olaparib or durvalumab + tremelimumab.	
12 Bone marrow findings consistent with MDS/AML.	

### Statistical analyses

Continuous variables will be summarized using descriptive statistics, i.e. number of subjects with available data (N), mean, median, standard deviation (S.D.), 25–75% quartiles (Q1-Q3) and range. Continuous variables could be transformed as categorical variable using median or using conventional cut-off from bibliography or clinical practice. If required comparison using Chi square (or exact Fisher test) or Student T test (or Wilcoxon Mann and Whitney) tests will be done. Categorical variables will be described by and percentages. The number of missing data will be described.

Each cohort will be described and analyzed separately.

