#### Sample size calculation

Sample size was determined using an A’Hern’s single stage design. The primary endpoint is progression PFS. It will be evaluated at 6 months (except for ovarian cancer with an evaluation at 18 months given the results of olaparib in SOLO-2 trial). The hypotheses are the following:
one-sided alpha risk =10%, a power = 90%,the expected rate of patients stable or in response after 6 weeks of olaparib is 80%,the expected rate of patients non-evaluable the primary endpoint is 5%,P0 and P1 are determined using hypotheses detailed above.

P0 is the highest level of inefficacy for which the new treatment will be rejected (maximal inefficacity). P1 defines the minimum required level of efficacy. The design of the trial focuses on demonstrating that this level is plausible given that the trial results and the efficacy is greater than the first proportion, P0. Taking into account these hypotheses: 270 patients will be included in the study, and at least 213 are required for statistical analyses. At the end the study, analysis of the primary endpoint will be performed on evaluable patients who were in response or stable after 8 weeks of olaparib.

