#### Analysis of efficacy endpoint(s)

Efficacy analyses will be performed in modified intent-to-treat population (ITT) population ie, all patients with a 6-month evaluation (12-month for ovarian cohort) and at least one dose of durvalumab + tremelimumab. Analyses will be repeated in the per protocol population (patients who had received all the planned doses).

6-month PFS rate (12 month-rate in the ovarian cohort) will be determined using the Kaplan Meier method. 95% Confidence interval (CI) will be provided. Patients alive without progression will be censored.

Median follow-up will be estimated using the reverse Kaplan Meier method.

PFS and Overall survival will be estimated using the Kaplan Meier method. Six-month, 1-year, 2-year rates as well as median OS and PFS will be reported with their 95% CI.

Disease control rates at 6 months will be determined and described with its 95% binomial CI. The same method will be applied to describe the response rate after 6 months of olaparib in each cohort.

All statistical analysis will be performed with SAS 9.4. In case of comparison, tests will be two-sided.

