#### Exploratory analyses

Analysis of immunogenicity will be performed based on IHC analysis. We will analyze the micro environment with T Cells and PD-L1 expression. Moreover, we will analyze immunogenic death with HMGB1 and LC3. These parameters will be compared before and after a target therapy to evaluate its impact on microenvironment.

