## Discussion

Among all solid tumors, a subgroup of patients presents a deficiency in homologous recombination repair genes. This abnormal DNA repair system sensitizes these tumors to PARP inhibitors. There is a strong rational to combine PARP inhibitors and immune checkpoint inhibitors. Indeed, PARP inhibitors induce DNA damage causing neoantigen increase, leading to a reinforced recognition by the immune system. Moreover, PARP inhibitors increase PD-L1 expression. In 2017, Lee et al have shown that anti-PD-L1 and olaparib combination is safe [12]. Recently, phase 2 MEDIOLA has shown promising results in BRCA mutated breast cancer with a control rate of 80% at 12 weeks [13]. In the light of these results, immunogenic target therapy with olaparib in combination with immune checkpoint inhibitors could act synergistically and might be a promising treatment in tumors with deficiencies in homologous recombination. Furthermore, blood, plasma and tumor tissue will be collected and assessed for potential prognostic and predictive biomarkers. Study is ongoing and the first patient was included in February 11th 2020.

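### The plan lets continuous variables be split at the sample median before testing, cohort by cohort; where used in exploratory or biomarker comparisons, this would lose power and give cut-offs that differ by chance

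*Protocol article*

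**What the plan says.** All references are to the protocol article.

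- Statistical analyses, on continuous variables: "Continuous variables could be transformed as categorical variable using median or using conventional cut-off from bibliography or clinical practice". The variables concerned, and the rule for choosing between the two kinds of cut-off, are not stated.
- Same paragraph, on tests: "If required comparison using Chi square (or exact Fisher test) or Student T test (or Wilcoxon Mann and Whitney) tests will be done". The list therefore contains tests for categories and tests on the continuous or rank scale, and both are conditional.
- Same section: "Each cohort will be described and analyzed separately".
- Analysis of efficacy endpoint(s): "In case of comparison, tests will be two-sided". No significance level is given for such comparisons.
- Exploratory analyses, on T cells, PD-L1, HMGB1 and LC3: "These parameters will be compared before and after a target therapy to evaluate its impact on microenvironment". No cut-off is mentioned there.
- Discussion: "blood, plasma and tumor tissue will be collected and assessed for potential prognostic and predictive biomarkers".
- Sample size calculation: "Sample size was determined using an A’Hern’s single stage design". The total is 270 included and at least 213 analysed, with no size per cohort.

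**The concern.** A median split treats a patient just above the cut the same as one far above it. The lost information has to be bought back with patients, and the separately analysed cohorts have few to spare. The median is also recalculated in each cohort. A label of high expression in one tumour type then need not mean the same marker level as in another, even if the underlying distributions are identical.

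The comparisons exposed are those that relate a continuous measurement to a group: the exploratory immune markers and any prognostic or predictive biomarker. A real association could be reported as absent, or a difference between tumour types could partly reflect where each median happened to fall. The same paragraph already names tests that avoid both problems.

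**Working it through.** **Figure to reproduce.** There is none. The article states no power for any comparison of a continuous or dichotomised variable.

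**Inputs from the article.** 213 analysed and 270 included patients; nine named tumour types; separate analysis by cohort; two-sided tests.

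**Assumptions, because the article gives no value.** Two-sided 5% level; normally distributed marker; equal cohorts, so 213/9 = 23.7 (about 24) analysed or 270/9 = 30 included, with 36 as a larger case; true difference d between two outcome groups of 0.5 to 1.5 SD; groups balanced 50:50 or 30:70.

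**Step 1: large samples.** A median split of a normal variable has relative efficiency 2/π = 0.637 against the t test, so the standardised signal shrinks by √0.637 = 0.798. With Φ the normal distribution function and z its quantile:

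power after split = Φ(0.798 × (1.96 + z[t-test power]) − 1.96)

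For 80%: 0.798 × (1.96 + 0.842) − 1.96 = 0.275, and Φ(0.275) = 61%.

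| t-test power | after median split | loss (points) |
|---|---|---|
| 50% | 35% | 15 |
| 60% | 42% | 18 |
| 70% | 51% | 19 |
| 80% | 61% | 19 |
| 90% | 73% | 17 |

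**Step 2: small cohorts.** Simulation, 4,000 runs per scenario: t test against median split followed by Fisher's exact test.

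| N | groups | d (SD) | t test | split + Fisher | loss (points) |
|---|---|---|---|---|---|
| 24 | 50:50 | 0.5 | 21% | 14% | 7 |
| 24 | 50:50 | 0.8 | 48% | 32% | 16 |
| 24 | 50:50 | 1.0 | 66% | 44% | 21 |
| 24 | 50:50 | 1.2 | 79% | 58% | 21 |
| 24 | 30:70 | 1.0 | 56% | 11% | 45 |
| 24 | 30:70 | 1.5 | 89% | 35% | 55 |
| 30 | 50:50 | 0.5 | 25% | 13% | 12 |
| 30 | 50:50 | 1.0 | 74% | 48% | 26 |
| 36 | 50:50 | 1.0 | 84% | 49% | 35 |

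The span for N = 24 to 36 is about 7 to 55 points. At d = 0.5 it is only about 7 to 18. Part of the larger losses comes from the discreteness of Fisher's test: its exact size after the split is 3.9% at N = 24 with 50:50 groups but 0.5% at N = 24 with 30:70.

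With uncorrected chi-square the loss ranges from none to about 29 points. Where it is small, the test is often oversized (exact size 9.4% at N = 36 with 50:50, 10.9% at N = 30 with 30:70). The Wilcoxon test stays close to the t test: 61% against 66% at N = 24, 50:50, d = 1.0.

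**Step 3: stability of the cut-off.** The standard error of a median in SD units is about √(π/2)/√n. At n = 24 this is 1.253/4.899 = 0.256 (simulated 0.249); at n = 36 it is 0.209 (simulated 0.205). Nine cohorts of 24 drawn from one identical distribution would have medians spread over 0.74 SD on average. A cut-off taken from the literature or clinical practice has no such spread.

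**Step 4: reach.** The primary endpoint is a Kaplan-Meier progression-free survival rate in a single-stage design for a proportion. The listed secondary endpoints are rates, times to event and toxicity grades. None requires a continuous variable to be split.

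**The case against.** The strongest reply is that the article only permits the split. Its wording is conditional, comparisons are made only if needed, and t and Wilcoxon tests stand in the same list. It does not say that a split variable must go to chi-square or Fisher; that link comes from reading two adjacent sentences together. Naming variables and cut-offs is ordinary work for an analysis plan, which is not shown. All of this stands, and it keeps the point minor. What remains is that the text expressly offers a median split as a route to testing. That is a stated option inferior to those beside it, not a missing detail.

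Three stronger readings are tempting and are not supported.

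- **A fixed loss, such as 20 to 45 points, as a property of this trial.** Cohort size, effect size, group balance and significance level are all assumed, and plausible inputs give less than 20 points or more than 45.
- **A median split planned for the before/after immune markers.** Exploratory analyses mentions no cut-off, and the general paragraph names only independent-sample tests. With 24 pairs, a 0.6 SD shift and correlation 0.5, a paired t test has about 80% power against about 34% for an exact McNemar test at the pooled median. However, neither that test nor a pooled median appears in the plan. The number of pairs is also unknown: the biopsies bracket olaparib, and participation needs a separate consent.
- **A cut-off chosen after seeing the results, or sample-dependent under both options.** The first cannot be established without the analysis plan. The second is wrong for conventional cut-offs.

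**Conclusion.** The point holds as a minor one. The article permits a median split before comparison within separately analysed cohorts. If the option is used, information is lost and the cut-off moves between cohorts by chance, by about 0.25 SD (one standard error) at an assumed 24 patients. The power cost is about 15-19 points in large samples when the t test has 50-90% power, and about 7 to 55 points with Fisher's test at 24-36 patients. These figures rest on a normal marker, a two-sided 5% level and assumed effect sizes, group balance and cohort sizes. They show what the option can cost and do not forecast a loss in this trial. The primary analysis, its stated power and the listed secondary endpoints are untouched.

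**What to change.** Replace the sentence on categorisation in Statistical analyses with text along these lines:

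> Continuous variables, including IHC markers, will be compared on their continuous scale by t test or a rank-based test; markers measured before and after treatment will be compared as within-patient change. Conventional clinical or literature cut-offs may be used for testing if they are named before the data are examined. Median categories will be used for description only.

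This keeps testing at established clinical cut-offs and all descriptive tables. A ban on every categorical comparison would go further than the problem requires. The cost is a short wording change, with no extra patients, samples or data.

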#### Sample size calculation

Sample size was determined using an A’Hern’s single stage design. The primary endpoint is progression PFS. It will be evaluated at 6 months (except for ovarian cancer with an evaluation at 18 months given the results of olaparib in SOLO-2 trial). The hypotheses are the following:
one-sided alpha risk =10%, a power = 90%,the expected rate of patients stable or in response after 6 weeks of olaparib is 80%,the expected rate of patients non-evaluable the primary endpoint is 5%,P0 and P1 are determined using hypotheses detailed above.

P0 is the highest level of inefficacy for which the new treatment will be rejected (maximal inefficacity). P1 defines the minimum required level of efficacy. The design of the trial focuses on demonstrating that this level is plausible given that the trial results and the efficacy is greater than the first proportion, P0. Taking into account these hypotheses: 270 patients will be included in the study, and at least 213 are required for statistical analyses. At the end the study, analysis of the primary endpoint will be performed on evaluable patients who were in response or stable after 8 weeks of olaparib.

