### Study objectives

The primary objective of the study is to evaluate the efficacy of olaparib + immunotherapy (durvalumab + tremelimumab) during 4 months, followed by durvalumab alone as maintenance treatment in patients with solid cancers and in response or stable, after prior molecular target therapy by olaparib based on molecular sequencing (mutation in homologous gene repair).

Study secondary objectives are:
To evaluate 6-month disease control rate (DCR) for all cohorts, except ovarian cohort which will be evaluated at 12-months.To evaluate 1 and 2-year PFS and overall survival (OS).To evaluate response rate after 6 weeks of olaparib therapy (STEP 1).To evaluate safety of molecular therapy by olaparib at the end of STEP1.To evaluate safety of molecular therapy (olaparib) + immunotherapy (durvalumab + tremelimumab) and immunotherapy in maintenance (durvalumab alone).

The study exploratory objective is to evaluate the immunogenic effect of olaparib (modification of immune infiltrate and immunogenic cell death markers on biopsy performed before and after olaparib treatment).

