### Study endpoints

The primary endpoint is progression free survival (PFS) 6 months after the initiation of immunotherapy for all cohorts, with the exception of ovarian cohort evaluated at 12 months. PFS is defined as the time from the date of first dose of immunotherapy to the date of progression or death from any cause. Progression will be defined using iRECIST criteria.

Secondary endpoints are:
Disease control rate, including stable and responsive disease, evaluated 6 months after immunotherapy initiation for all cohorts except ovarian cohort, evaluated at 12 months.Overall survival (OS) evaluated at 12 and 24 months after immunotherapy initiation defined by the time of the first immunotherapy dose to the date of death from any cause.Response rate evaluated by CT scan, RECIST evaluation after 6 weeks of olaparib therapy.Olaparib toxicity evaluated at the end of STEP1 using CTCAE V5.Olaparib + immunotherapy (tremelimumab + durvalumab) toxicity evaluated at 3, 6 and 12 months after immunotherapy initiation using CTCAE V5.

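### The sample-size section evaluates the ovarian cohort's primary PFS endpoint at 18 months, but the endpoint and analysis sections evaluate it at 12 months; the time point behind the ovarian P0 and P1 must be settled.

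*Protocol article*

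**What the plan says.** Three sections of the protocol article give a time for the ovarian cohort's primary endpoint.

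- **Study endpoints:** this section defines it by the words "progression free survival (PFS) 6 months after the initiation of immunotherapy for all cohorts, with the exception of ovarian cohort evaluated at 12 months". The clock starts at the first dose of immunotherapy.
- **Analysis of efficacy endpoint(s):** the modified ITT population is "all patients with a 6-month evaluation (12-month for ovarian cohort) and at least one dose of durvalumab + tremelimumab", and "6-month PFS rate (12 month-rate in the ovarian cohort) will be determined using the Kaplan Meier method".
- **Sample size calculation:** PFS is again named as the primary endpoint, evaluated at 6 months "except for ovarian cancer with an evaluation at 18 months given the results of olaparib in SOLO-2 trial".

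The sample-size section also says "Sample size was determined using an A’Hern’s single stage design", with a one-sided alpha of 10% and power of 90%. It says that P0 and P1 follow from the listed hypotheses but prints no values for any cohort. The totals are 270 patients included and 213 for analysis. The Statistical analyses section has each cohort analysed separately.

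For the secondary disease control rate (DCR), the Study objectives section says "To evaluate 6-month disease control rate (DCR) for all cohorts, except ovarian cohort which will be evaluated at 12-months", and the Study endpoints section agrees. The efficacy analysis section says only "Disease control rates at 6 months will be determined and described with its 95% binomial CI".

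**The concern.** An A'Hern design is an exact binomial rule: a cohort succeeds if at least r of n patients meet the endpoint. Its n and r give the stated error rates only for the proportion to which P0 and P1 refer. The proportion progression-free at 12 months cannot be lower than at 18 months, and with any events in between it is higher, so one P0/P1 pair cannot serve both times.

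Read literally, the ovarian cohort was sized on an endpoint that the analysis section never estimates. The further PFS and OS rates there are at 6 months, 1 year and 2 years. Because cohorts are analysed separately, no other cohort can make up for a miscalibrated ovarian decision. In a single-arm, open-label cohort that decision rests wholly on the comparison with P0.

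**Working it through.** **1. The plan's own figure.** The A'Hern derivation of 213 cannot be reproduced, because no P0, P1, cohort size or cut-off is printed. Only the inflation can be checked. With the stated 80% entering STEP 2, 213/0.80 = 266.25, so 267, close to 270. Adding the stated 5% non-evaluable rate gives 213/(0.80 × 0.95) = 280.3, so 281. Thus 270 fits the 80% rate alone. This does not show which ovarian time point was used.

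**2. Could a different starting point explain 18 against 12?** The primary endpoint counts from first immunotherapy. STEP 1 lasts 6 weeks (8 weeks in some sentences). Adding that to 12 months gives about 14 months, not 18.

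**3. Illustration.** Inputs from the document: one-sided alpha 0.10, power 0.90, exact single-stage design. Assumed: the P0/P1 pairs and an exponential PFS curve.

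- Design: the smallest n with a cut-off r such that P(X ≥ r | n, P0) ≤ 0.10 and P(X ≥ r | n, P1) ≥ 0.90, X binomial.
- From 18 to 12 months: S(12) = S(18)^(2/3). For example, 0.40^(2/3) = 0.543.
- From 12 to 18 months: S(18) = S(12)^1.5. For example, 0.60^1.5 = 0.465.
- Type I error if a cut-off set at 18 months is applied to 12-month status: P(X ≥ r | n, P0^(2/3)).
- Power if the pair was set at 12 months but the test is made at 18: P(X ≥ r | n, P1^1.5).

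| Assumed P0/P1 | n, r | Type I error, 18-month cut-off at 12 months | Power, 12-month design at 18 months | n, r for the same curves when an 18-month pair is moved to 12 months |
|---|---|---|---|---|
| 0.30/0.45 | 71, 27 | 0.90 | 0.10 | 84, 44 |
| 0.30/0.50 | 39, 16 | 0.74 | 0.28 | 49, 27 |
| 0.40/0.60 | 41, 21 | 0.71 | 0.33 | 58, 37 |
| 0.50/0.70 | 39, 24 | 0.64 | 0.42 | 58, 42 |
| 0.30/0.55 | 25, 11 | 0.61 | 0.45 | 33, 19 |
| 0.40/0.65 | 29, 16 | 0.54 | 0.46 | 36, 24 |
| 0.50/0.75 | 26, 17 | 0.49 | 0.57 | 36, 27 |

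**4. If only the cut-off is corrected.** Take an 18-month pair of 0.40/0.60 with n = 41. At 12 months the pair becomes 0.543/0.711. The smallest cut-off with error at most 0.10 is then 27, since P(X ≥ 27 | 41, 0.543) = 0.09, and the power is P(X ≥ 27 | 41, 0.711) = 0.82. In this case, re-deriving the cut-off at an unchanged size restores the error rate but not the full 90% power.

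**The case against.** The strongest reply is that 18 may simply be wrong in one sentence. The endpoint definition, the modified ITT definition and the Kaplan-Meier rate all say 12 months. If the calculation was made at 12 months, the 10% error and 90% power are intact and only a word needs changing. Nothing printed rules this out, and the ovarian P0, P1, size and cut-off would normally stand in the full protocol, which is not shown. This stands: the statistical consequence is conditional. It does not remove the contradiction, and the benchmark-trial reason attached to 18 months makes a plain typing slip less certain.

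The numbers are also open to challenge. The pairs and the exponential curve are assumed, and the illustration supposes that a cut-off would be carried unchanged from one time point to the other, which no section says. That also stands. The ranges show how sensitive such a rule is to the time point; they are not estimates or bounds for this trial.

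Two stronger readings are tempting. A reader might infer that the study objectives also fix the primary endpoint at 12 months; they do not, because the primary objective names no time and the 12 months there belongs to the secondary DCR. A reader might also infer that the time point is free to be chosen after the data are seen. The endpoint and analysis sections consistently point to 12 months, so the documents do not support that.

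**Conclusion.** The contradiction is real, stands in current text and concerns a primary endpoint: 18 months in the sample-size section against 12 months in the endpoint and analysis sections. It affects one of nine cohorts and should be corrected before that cohort is analysed.

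If the sample-size section describes the calculation actually made, the ovarian rule does not have its stated error and power for the 12-month rate. Over the assumed pairs the departure is large in every case: type I error of about 0.49 to 0.90 instead of 0.10, or, in the reverse mismatch, power of about 0.10 to 0.57 instead of 0.90. A reader might conclude that the ovarian cohort has certainly lost its stated operating characteristics. The document does not support that, because it prints none of the design values that would show which time point was used.

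The DCR sentence is a separate and minor inconsistency. DCR is secondary and descriptive, with no test or sizing attached, and adds nothing to the weight of the main point.

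**What to change.** 1. Reconcile the Study endpoints, Sample size calculation and Analysis of efficacy endpoint(s) sections to one ovarian time point. Twelve months is the one already in the endpoint and analysis sections.
2. State the time point for which the ovarian P0 and P1 were set.
3. If it is not the time point to be analysed, re-derive P0, P1 and the cut-off at the analysed time point before any ovarian outcome is analysed, and restate the power that the planned ovarian cohort then has. If it is the same, correcting the sample-size sentence is enough.
4. Add the 12-month ovarian exception to the DCR sentence in the efficacy analysis section.

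The cost is a text correction and, at most, one recalculation. The restated power may be less favourable than 90%.

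### The ovarian cohort's primary PFS landmark is 18 months in the sample-size section but 12 months in the endpoint and analysis sections; the plan must settle on one and confirm that the design was derived for it

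*Protocol article*

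**What the plan says.** Under Sample size calculation, the protocol article states: "Sample size was determined using an A’Hern’s single stage design". One-sided alpha is 10% and power 90%. PFS is to be evaluated at 6 months, "except for ovarian cancer with an evaluation at 18 months given the results of olaparib in SOLO-2 trial".

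Every other place uses 12 months for the ovarian cohort:

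- Study endpoints, primary endpoint: "with the exception of ovarian cohort evaluated at 12 months".
- Analysis of efficacy endpoint(s), population: "all patients with a 6-month evaluation (12-month for ovarian cohort) and at least one dose of durvalumab + tremelimumab".
- Analysis of efficacy endpoint(s), primary estimate: "6-month PFS rate (12 month-rate in the ovarian cohort) will be determined using the Kaplan Meier method".
- Study objectives, disease control rate (secondary): "except ovarian cohort which will be evaluated at 12-months".

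The list of survival rates to be reported contains no 18-month figure: "Six-month, 1-year, 2-year rates as well as median OS and PFS will be reported with their 95% CI". No sentence reconciles 18 with 12 months.

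**The concern.** An A'Hern design ties four quantities (P0, P1, n and the number of successes required) to one binary outcome at one time point. PFS at 12 months cannot be lower than PFS at 18 months in the same patients. A cut-off built for 18 months is therefore too lenient at 12, and one built for 12 months is too strict at 18.

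The article says that each cohort is analysed separately, so any error falls wholly on the ovarian conclusion. While two landmarks stand in the plan, the choice between them could also be made after the data are seen.

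**Working it through.** **1. What can be reproduced.** The only printed sizes are totals over all cohorts: 270 included and 213 for analysis. With 80% expected to be stable or responding after olaparib, 270 × 0.80 = 216, close to 213. This says nothing about the ovarian landmark. The ovarian P0, P1, n and cut-off are not printed, so that design cannot be reproduced.

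**2. Could a different time origin explain the gap?** Study endpoints says: "PFS is defined as the time from the date of first dose of immunotherapy to the date of progression or death from any cause". Counting from the start of olaparib instead would add the lead-in, which the article puts at 6 to 8 weeks. Twelve months plus 8 weeks is about 14 months, not 18.

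**3. Size of the effect if the landmarks are mixed.** This is an illustration, because the article gives no P0 or P1.

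- Assumed P0/P1 pairs: nine, with differences of 15, 20 and 25 points.
- Design: smallest n, with cut-off r, such that P(X ≥ r | n, P0) ≤ 0.10 and P(X ≥ r | n, P1) ≥ 0.90, X exact binomial.
- Constant hazard: S(12) = S(18)^(12/18) and S(18) = S(12)^(18/12).

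Case A: the pair holds 18-month rates and the result is read at 12 months. Type I error = P(X ≥ r | n, P0^(2/3)).

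Case B: the pair holds 12-month rates and the result is read at 18 months. Power = P(X ≥ r | n, P1^1.5).

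The last column re-derives the case A design at 12 months, using P0^(2/3) and P1^(2/3).

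| P0 / P1 | n, r | Case A: type I error | Case B: power | Re-derived n, r |
|---|---|---|---|---|
| 0.30 / 0.55 | 25, 11 | 0.61 | 0.45 | 33, 19 |
| 0.40 / 0.65 | 29, 16 | 0.54 | 0.46 | 36, 24 |
| 0.50 / 0.75 | 26, 17 | 0.49 | 0.57 | 36, 27 |
| 0.30 / 0.50 | 39, 16 | 0.74 | 0.28 | 49, 27 |
| 0.40 / 0.60 | 41, 21 | 0.71 | 0.32 | 58, 37 |
| 0.50 / 0.70 | 39, 24 | 0.64 | 0.42 | 58, 42 |
| 0.55 / 0.75 | 39, 26 | 0.60 | 0.48 | 51, 39 |
| 0.40 / 0.55 | 75, 36 | 0.89 | 0.13 | 96, 59 |
| 0.50 / 0.65 | 72, 42 | 0.83 | 0.19 | 99, 69 |

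Worked example, 0.40/0.60: n = 41 with at least 21 successes gives alpha 0.097 and power 0.903. Under constant hazard, an 18-month PFS of 0.40 means a 12-month PFS of 0.40^(2/3) = 0.543, and P(X ≥ 21 | 41, 0.543) = 0.71. In reverse, 0.60^1.5 = 0.465, and P(X ≥ 21 | 41, 0.465) = 0.32.

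**4. Keeping n and moving only the cut-off (case A).** For the same pair the 12-month rates are 0.543 and 0.711. With n = 41, the smallest cut-off holding alpha at 0.10 is 27: P(X ≥ 27 | 41, 0.543) = 0.09, and power is P(X ≥ 27 | 41, 0.711) = 0.82. Re-deriving for 90% power takes n from 41 to 58. Over the 20- and 25-point pairs n rises by 7 to 19 (29 to 36 at the least, 39 to 58 at the most); the two 15-point pairs rise by 21 and 27.

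**The case against.** The strongest reply is that 18 months is a drafting slip and the design is sound. Twelve months appears in the objectives, the endpoints, the population and the primary estimate; 18 appears once. The statistical sections contain other timing slips: the sample-size section refers to both 6 and 8 weeks of olaparib, and the efficacy section speaks of response after 6 months of olaparib where the objectives say 6 weeks. If P0 and P1 were 12-month rates, alpha and power hold and one phrase needs correcting.

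That reading is possible but cannot be assumed. The 18-month figure carries its own reason, the olaparib results in SOLO-2, and stands in the section that fixes the design.

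The reply does rule out a stronger reading. A reader might infer that the ovarian cut-off and size are in fact set for a different endpoint, and that the test lacks its stated alpha and power. The article does not show this: it prints no ovarian P0, P1, n or cut-off, and a condensed article may leave these to the full protocol. Nor does the efficacy section state that a success count is compared with a cut-off at 12 months; it describes a Kaplan-Meier rate with a 95% confidence interval. The cut-off is implied by the choice of an A'Hern design.

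Condensation does not excuse the contradiction itself. The article does not omit the landmark; it states two.

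**Conclusion.** The inconsistency is certain and concerns the primary endpoint of one cohort. At least one statement, in the sizing or in the endpoint and analysis sections, is wrong as written. No calculation in the article is shown to be incorrect.

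The statistical consequence is conditional:

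- P0/P1 set for 18 months, result read at 12: the 10% one-sided alpha does not hold. Illustrative type I error is about 0.5 to 0.9.
- P0/P1 set for 12 months, result read at 18: the 90% power does not hold. Illustrative power is about 0.1 to 0.6.
- P0/P1 set for 12 months, result read at 12: only the wording of the sample-size section is wrong.

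The ranges rest on assumed P0/P1 pairs 15 to 25 points apart and a constant hazard. The direction does not depend on the pair chosen, but the size does, so the figures are not estimates for this trial. The correction is needed in all three cases, because the text alone does not show which applies.

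**What to change.** First, confirm from the design file which landmark the ovarian P0, P1, n and cut-off were derived for. Then state that one landmark in Study endpoints, Sample size calculation and Analysis of efficacy endpoint(s), covering the primary endpoint, the sizing, the modified intent-to-treat population and the PFS rate.

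- Derived for 12 months and 12 kept: change the phrase in the sample-size section. No recalculation.
- Derived for 18 months and 18 kept: change the primary endpoint, the population and the PFS rate to 18 months, and add an 18-month rate to those reported. No recalculation.
- Derived for 18 months and 12 kept: re-derive P0, P1 and the cut-off at 12 months, restate either the ovarian n or the power achieved with the planned n, and update the 213 and 270 totals if n changes.

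The first two cost a text correction. In the third, holding 90% power would add about 7 to 19 evaluable ovarian patients in the illustrative 20- to 25-point cases. Recruitment has begun, so keeping the planned n and restating the achieved power is the cheaper option. The landmark should be fixed before any ovarian efficacy data are examined.
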